## Abstract

Supplemental Digital Content is available in the text

## Introduction

1

The prevalence of obesity and related diseases has steadily increased among Korean adults. Obesity is associated with increasing risks for type 2 diabetes mellitus (T2DM), hypertension (HTN), metabolic syndrome, and other dyslipidemia diseases. According to previous studies, the prevalence of obesity increased from 29.7% to 32.4% from 2009 to 2015, with an estimated cost of $ 1.8 billion as per for available 2015 data.^[1–3]^

Various therapeutic strategies using conventional medications to treat or prevent obesity have been proposed, including many of their side effects which may limit their use.^[4]^ Complementary and alternative medicine (CAM) may offer some promise here as the beneficial effects of herbal medicine on obesity have been reported.^[5]^

Therefore, research is needed not only to confirm effective in obesity but also, the safety of use in human clinical studies. *Daesiho-tang* (DSHT) is a herbal formulation in traditional Korean medicine; it has been registered and authorized for use in Korea by the Korea Food & Drug Administration. According to the *Donguibogam*, it is used for the treatment of acute febrile illness, acute pneumonia, habitual constipation, and chronic gastritis.^[6]^ The anti-obesity effect of DSHT has been shown in preclinical studies. Obesity-induced mice in the DSHT group showed greater reductions in the body weight, and liver and fat tissue mass when compared with the control group. In hematological experiments, total cholesterol (TC), triglyceride (TG), glucose tolerance, and HDL cholesterol were significantly reduced in high-fat diet-fed mice. Quantitative analysis of denaturing gradient gel electrophoresis (DGGE) showed that bacterial gene expression in HFD mice was significantly increased in the DSHT treated group. As a result of measuring liver tissue using RT2 PCR, it was observed that several genes in the DSHT treatment group regulated cholesterol metabolism by expressing them up and down.^[7]^

*Chowisengcheong-tang* is an anti-obesity herbal medicine for *Taeeumin* made by *Dongeuisusaebowon*.^[8]^ It is currently marketed under the approval of KFDA for the treatment of abdominal bloating and distention after meals, and leg muscle weakness. According to findings of previous human subject studies, significant weight loss was achieved after receiving combined treatment with electro acupuncture and CST.^[9]^ However, the effect of CST alone on obesity has not yet been confirmed in clinical studies.

There is either a lack of or inadequate reporting of the scientific evidence of the effects of DSHT and CST on obesity in clinical studies. This clinical trial is intended to help fill this gap by evaluating the effectiveness and safety of the 2 herbal medicines DSHT and CST in obesity. We designed a randomized, placebo-controlled, multi-center, clinical trial to evaluate the efficacy and safety of the pharmacological intervention, DSHT and CST on obese women with high risk for metabolic syndrome.

## Methods/design

2

### Study design

2.1

This trial is a randomized, double-blinded, three-arm, placebo-controlled, multi-center, study that will be conducted at the following sites: Gachon University Gil Korean Medical Hospital, Dongguk University Ilsan Oriental Hospital, and Sangji University Oriental Medical Center. The total study duration is approximately 13 weeks from the screening visit. A schedule of this study flow is shown in Table 1.

**Table 1 T1:**
[figure not shown]
Study flow of the trial.

## Study objectives

3

The main objective is to evaluate the efficacy and safety of DSHT and CST on obese Korean women with high risk for metabolic syndrome.

### Recruitment

3.1

The study participants will be recruited through advertisement for human research study which includes the following information: the purpose of the study, study duration, eligibility criteria, and the detailed information on the investigational drugs. The advertisement notice, posted on bulletin boards inside and outside the hospitals, will invite potential study participants to voluntarily contact the site trial staff for eligibility assessment.

### Participants

3.2

#### Inclusion criteria

3.2.1

Criteria for inclusion of participants are as follows:

1.Females aged 18 to 65 years.2.Patients who have any of the following conditions:1)BMI 30 kg/m^2^ or over;2)BMI 25 to 29.9 kg/m^2^, who have at least one of the following risk factors;Patients who have been diagnosed with hypertension and currently under adequate treatment with antihypertensives, or individuals with systolic blood pressure (SBP) ≥140 mmHg and diastolic blood pressure (DBP) ≥90 mmHg at the screening visit.Patients who have been diagnosed with T2DM and are currently on adequate treatment or individuals with fasting blood glucose >126 mg/dL at the screening visit.Patients who have been diagnosed with hyperlipidemia and are currently under adequate treatment, or individuals with total cholesterol ≥200 mg/dL or triglycerides ≥150 mg/dL at screening visit.3.Subjects who have agreed to a low-calorie diet during the trial.4.Patients who have signed the written informed consent form.

### Exclusion criteria

3.3

Criteria for exclusion of participants are as follows:

1.Patients with endocrine diseases such as hypothyroidism, Cushing syndrome, etc, which can affect the weight readings.2.Patients with cardiovascular diseases, such as, heart failure, angina pectoris, myocardial infarction, and stroke.3.Patients with uncontrolled hypertension with SBP >145 mmHg or DBP >95 mmHg.4.Patients with severe renal or liver impairment (serum creatinine [SCr] > 2.0 mg/dL or 2.5 times higher than the maximum values of alanine transaminase [ALT], aspartate aminotransferase [AST], and alkaline phosphatase [ALP] in patients with normal renal and liver function.).5.Patients with a surgical history for weight reduction such as bariatric surgery.6.Patients with history of or current eating disorder such as anorexia nervosa or bulimia nervosa.7.Patients who have experienced a 10% weight reduction within the past 6 months.8.Those who decided to stop smoking within the last 3 months or who have an irregular smoking habit.9.Patients with cholelithiasis.10.Patients with narrow angle glaucoma.11.Patients receiving treatment with controlled substances including antidepressants, antiserotonins, barbiturates, antipsychotics, Central nervous system stimulants.12.Patients on any medications that may have an effect on absorption, metabolism, and excretion of drugs and weight within the last 3 months; these include appetite suppressants, laxatives, oral steroids, thyroid hormone, amphetamine, cyproheptadine, and phenothiazine.13.Patients who are in the childbearing age and do not agree to use effective contraceptive methods during the study period.14.Patients who have participated in any clinical trial within the past month.15.Patients judged unable to follow instructions of the trial by clinical trial investigators.

### Subject withdrawal criteria

3.4

The subject withdrawal criteria are as follows: detection of eligibility violations; occurrence of a serious adverse event; subject has an acute reaction (such as allergy or shock) due to administration of the investigational product; detection of a systemic disease that was not discovered at the screening; <70% adherence rate; subject's withdrawal of consent; use of any forbidden medication or treatment during the trial that could affect the study result; uncooperative subject; occurrence of other significant protocol violations; subject who cannot follow up; subject unable to progress because of worsening of pre-existing disease; investigator's decision to terminate the process for the sake of the subject's health. The participants who are withdrawn after randomization will be followed up to examine outcomes.

### Sample size

3.5

This trial is a pilot study to examine the feasibility of a full randomized controlled trial for evaluating the efficacy and safety of DSHT and CST in obesity and to determine the effect size for further large-scale studies. A sample cohort comprising of 120 patients have been considered after assessing their frequency of clinic visits, availability of study staff, funding availability, and dropout rates at each participating site.

### Randomization and blinding

3.6

The Institute of Safety, Efficacy, and Effectiveness Evaluation for Korean Medicine (ISEE), the Contract Research Organization (CRO), will generate random sequences using the R program. Randomization number assignment via the web-based system will be performed at visit 2 by the clinical research coordinator (CRC) or research assistants at each site. The subjects in this trial will be assigned to one of three groups with an allocation ratio of 1:1:1. All participants, investigators, and monitors will be blinded. No one, with the exception of the statisticians at ISEE, will be aware of which random numbers refer to either of the treatment groups or the placebo group. The randomization table kept in the opaque sealed envelope by the CRO will be opened according to Standard Operating Procedures (SOPs).

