### Interventions

3.8

In this trial, we plan to use DSHT from Hanpoong Pharm & Foods Co., Ltd., and CST from Hanjoong Pharmaceutical company. The placebo production, IP repackage, and IP distribution process were performed by Hanpoong Pharm & Foods Co., Ltd.

DSHT consists of 8 medicinal herbs: Paeoniae radix (1.00 g), Scutellariae radix (1.00 g), Bupleuri radix (2.0 g), Pinelliae rhizome (1.33 g), Zingiberis rhizome (1.67 g), Rhei undulati rhizome (0.67 g), Zizyphus fructus (1.00 g), and Ponciri fructus (0.67 g).

CST consists of 12 medicinal herbs: Coicis Semen (3.75 g), Castanea mollissima (3.75 g), Raphani Semen (1.875 g), Epedrae Herba (1.25 g), Platycodi Radix (1.25 g), Liliopis Tuber (1.25 g), Schizandrae Fructus (1.25 g), Acori Rhizoma (1.25 g), Polygalae Radix (1.25 g), Asparagi Radix (1.25 g), Zizyphi Semen (1.25 g), Longanae Arillus (1.25 g).

Each raw material will be manufactured in Hanpoong and Hanjoong, respectively, and both will be collected and packaged as IP by Hanpoong Pharm & Foods Co., Ltd.

The placebo product consists of lactose, corn starch, and food colorings, and possesses an appearance, shape, weight, taste, and color similar to DSHT and CST. The treatment drug and placebo will be supplied by Hanpoong Pharm & Foods Co., Ltd.

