#### Efficacy assessment

3.13.1

The demographic data at the baseline will be analyzed using a *t* test for continuous data and a chi-square test for categorical data. Analysis of the primary endpoint will be performed using intention-to-treat (ITT) datasets. Per-protocol (PP) datasets will also be analyzed as a reference. The term ITT dataset refers to a set of data regarding all randomly assigned participants. Missing data will be assigned using the last-observation-carried-forward (LOCF) analysis method. PP datasets include data on only the participants who completed the trial with no protocol violations or deviations.

The secondary endpoint data will be analyzed using both ITT and PP datasets. The average weight change before and after treatment will be analyzed using a paired *t* test for intragroup data and a Student *t* test for intergroup data. The average weight during the treatment phase will be analyzed using repeated measures analysis of variance (ANOVA) tests. Other secondary data will be analyzed identically to the average weight change, with the exception of glucose measurements and questionnaire results, which will be compared only before and after treatment between the groups. We also use ANOVA tests to analyze subgroups of QSCC II and OPIQ. The present study has no plan for an interim analysis.

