### Data and safety monitoring

3.15

The ISEE will monitor the clinical trial. The monitoring will begin once the first participants complete the required number of visits. All investigational institutions will be monitored based on the SOPs while this trial is in process. Auditing is not scheduled for the present study. To improve data quality, range checks for data values and double data entry will be conducted. Any other committee such as a coordinating center, steering committee, or endpoint adjudication committee will not be applicable to the present study.

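### The blinding section exempts the CRO's statisticians as a group, without limit of role or time, so per-protocol membership and analytic choices are not shielded from knowledge of the arm

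*Protocol article*

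**What the plan says.** All references are to the protocol article.

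- **Randomization and blinding (3.6).** ISEE is the CRO, and "the Contract Research Organization (CRO), will generate random sequences using the R program". On who is blinded: "All participants, investigators, and monitors will be blinded". Statisticians are not in that list. The exemption follows: "No one, with the exception of the statisticians at ISEE, will be aware of which random numbers refer to either of the treatment groups". The section closes with custody of the list: "The randomization table kept in the opaque sealed envelope by the CRO will be opened according to Standard Operating Procedures (SOPs"). It gives no time point for opening.
- **Data and safety monitoring (3.15).** "The ISEE will monitor the clinical trial". No audit is scheduled, and no steering or endpoint adjudication committee applies.
- **Efficacy assessment (3.13.1).** "Analysis of the primary endpoint will be performed using intention-to-treat (ITT) datasets", and ITT means everyone randomized. PP is a reference analysis for the primary endpoint, while secondary endpoints are analysed on both sets. On PP membership: "PP datasets include data on only the participants who completed the trial with no protocol violations or deviations".
- **Subject withdrawal criteria (3.4).** Some reasons are open-ended, such as lack of cooperation or other significant violations.

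**The concern.** A CRO statistician has to know the code in order to generate it. The difficulty is that the text gives this knowledge to the CRO's statisticians collectively, and they are the only statisticians the article mentions. On the page, whoever cleans, classifies or analyses the data as a statistician may already hold the code.

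That matters where a decision needs judgement. PP membership does: someone must decide whether an event counts as a deviation, and some withdrawal reasons are matters of opinion. Choices such as how to query an outlying weight are also open to influence if the person making them knows the arm. The trial is described as a pilot meant to supply an effect size for larger studies (Sample size, 3.5), so a distorted PP estimate could be carried into later planning.

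**Working it through.** The plan states no figure on this point, so there is nothing to reproduce. The check is a reading of the sections against each other, followed by one illustration on assumed inputs.

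**Step 1: who may know the arm.** Section 3.6 lists three blinded parties and one exempt party. The exempt party is plural and is restricted neither by role (list generation or analysis) nor by time (before or after lock).

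**Step 2: the sealed envelope.** The next sentence of 3.6 keeps the table sealed at the CRO until opened under the SOPs. If the statisticians already know which numbers belong to which arm, the seal does not protect against them. If the seal does bind them, the exemption is too wide. The two sentences need one reading, and the text does not supply it.

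**Step 3: which decisions are exposed.**

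| Item | How it is decided | Exposed to knowledge of the arm? |
|---|---|---|
| ITT membership | all randomized | no |
| Safety set membership (3.14) | dosed at least once | no |
| PP membership | completed, with no violation or deviation | yes, if the person deciding holds the code |
| Queries and analytic choices | not described | yes, on the same condition |

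**Step 4: who decides.** No section says who classifies PP or who runs the analysis. The condition in the last two rows is therefore neither met nor excluded by the text.

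**Step 5: hypothetical worst case.** The allocation gives 120 / 3 = 40 women per arm. Everything else here is an assumption and appears nowhere in the document: no drug effect, normally distributed weight change, 8 or 12 women per arm with a borderline deviation, and 4 of them excluded by someone who knows both arm and outcome (the least favourable on active, the most favourable on placebo). The 36 remaining in an arm then shift by the sum of the four most extreme expected normal order statistics, divided by 36:

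- 4 of 8: (1.4236 + 0.8522 + 0.4728 + 0.1525) / 36 = 2.9011 / 36 = 0.081 SD in one arm, and 2 × 0.081 = 0.16 SD for the contrast.
- 4 of 12: (1.6292 + 1.1157 + 0.7928 + 0.5368) / 36 = 4.0745 / 36 = 0.113 SD in one arm, and 2 × 0.113 = 0.23 SD for the contrast.

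A simulation of 20,000 trials on the same assumptions puts the false-positive rate of a nominal 5% two-sample t test at about 10% (4 of 8) and 16 to 17% (4 of 12). With exclusions in the active arm only, it is about 6% and 8%. If the exclusions are made blind to arm, the expected bias is 0. These figures describe deliberate selection; they do not forecast what would happen in this trial.

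**The case against.** The strongest reply is that the document describes no biasing step. It does not say that the ISEE statisticians judge PP membership, raise queries or run the analysis. The parties it does describe as working with sites and data are blinded, and Ethics and dissemination (3.16) reserves the right of data access to investigators. Blinded data review and the timing of PP decisions commonly belong in the SAP or full protocol, so their absence from an article is no defect. The PP rule is also strict: with no major/minor threshold, a recorded deviation excludes, which leaves less room for choice. And because ITT stands beside PP throughout, a distorted PP result would tend to show as a divergence.

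Most of this stands, and it limits the point. It does not remove it, because the article is not silent. It states a rule that gives statisticians as a group knowledge of the code, and an SAP requiring blinded analysts would have to contradict that rule.

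Three stronger readings are tempting but unsupported:

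- *That ISEE's monitoring role unblinds the monitors.* Section 3.6 says monitors are blinded. Having code holders and monitors in one CRO is organizational proximity, not a stated breach.
- *That the statisticians know every allocation from the first patient.* An exemption without a time limit invites this reading, but the text does not say so and the sealed envelope pulls the other way.
- *That the DSHT manufacturer also knows the code.* Section 3.8 says "The placebo production, IP repackage, and IP distribution process were performed by" that company, but not that packing was done by random number. Custody of pack codes is a detail an article may leave out.

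**Conclusion.** The point holds in a limited form. Section 3.6 sets an exemption wider than list generation requires, gives it no end point, and leaves it unreconciled with the sealed table. The consequence is confined to PP results and to choices made by any analyst who holds the code. A reader might infer that the trial's analysis sets in general, or its primary result, are compromised. The documents do not support that: ITT and safety membership is mechanical, and the primary analysis is on ITT.

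The size cannot be estimated from the document. The 0.16 to 0.23 SD in the illustration is a ceiling for one assumed pattern of deliberate exclusion, and the expected bias with blinded exclusion is zero. The conclusion rests on reading the plural exemption as it is written, and on the absence of any statement here that the people who classify PP or analyse the data are blinded. The change is worth making because it is cheap and replaces a stated rule with a safer one.

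**What to change.** Reword section 3.6 so that:

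1. Before database lock, only the ISEE statistician who generates the list knows the code, and that person takes no part in data queries, PP classification or analysis.
2. The sealed table is opened only after PP membership has been fixed blind to arm and the database is locked, apart from emergency unblinding under the SOPs.

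This also settles how the exemption and the sealed envelope fit together. The article already refers to statisticians in the plural, so separating the roles should not need extra staff. The cost is the rewording and a short blinded review of PP membership, which slightly delays the lock and the release of the code.

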### Study procedures

3.7

After enrollment, participants will be receiving the assigned Investigational product (IP) and will be prohibited from taking any drugs which can affect weight loss for 12 weeks. The IP will be orally administered as 6 g of the given granules to be taken with water 3 times a day after meals. The daily dosage of both IPs is based on the Ministry of Food and Drug Safety (MFDS) guidelines. The study participants will be asked to return any remaining drugs at 4 weekly intervals to assist in the determination of adherence.

### Interventions

3.8

In this trial, we plan to use DSHT from Hanpoong Pharm & Foods Co., Ltd., and CST from Hanjoong Pharmaceutical company. The placebo production, IP repackage, and IP distribution process were performed by Hanpoong Pharm & Foods Co., Ltd.

DSHT consists of 8 medicinal herbs: Paeoniae radix (1.00 g), Scutellariae radix (1.00 g), Bupleuri radix (2.0 g), Pinelliae rhizome (1.33 g), Zingiberis rhizome (1.67 g), Rhei undulati rhizome (0.67 g), Zizyphus fructus (1.00 g), and Ponciri fructus (0.67 g).

CST consists of 12 medicinal herbs: Coicis Semen (3.75 g), Castanea mollissima (3.75 g), Raphani Semen (1.875 g), Epedrae Herba (1.25 g), Platycodi Radix (1.25 g), Liliopis Tuber (1.25 g), Schizandrae Fructus (1.25 g), Acori Rhizoma (1.25 g), Polygalae Radix (1.25 g), Asparagi Radix (1.25 g), Zizyphi Semen (1.25 g), Longanae Arillus (1.25 g).

Each raw material will be manufactured in Hanpoong and Hanjoong, respectively, and both will be collected and packaged as IP by Hanpoong Pharm & Foods Co., Ltd.

The placebo product consists of lactose, corn starch, and food colorings, and possesses an appearance, shape, weight, taste, and color similar to DSHT and CST. The treatment drug and placebo will be supplied by Hanpoong Pharm & Foods Co., Ltd.

### Primary outcome measurement

3.9

The primary outcome is to evaluate the changes in mean body weight in the DSHT and CST groups compared with the placebo group and determine their statistical significance, if any, after 12 weeks.

### Secondary outcome measurements

3.10

The secondary outcomes will focus on changes of following obesity related measurements between baseline and post treatment: mean weight reduction, body mass index (BMI), body fat, waist and hip circumferences, lipid profile, C-Reactive protein (CRP), volume of visceral fat, Korean version of Obesity-related Quality of Life (KOQoL), The Korean Version of Eating Attitudes Test-26 (KEAT-26).

KOQoL is a validated outpatient-based quality of life assessment questionnaire on obese patients. It consists of 6 areas (psychosocial health, physical health, work and family affairs, daily life, sexual relationships, and relationship with food) with a total of 15 items. Each item is a 4-point Likert Scale ranging from “absolutely not” (1 point) to “always” (4 points). The total maximum score is 60 points. Higher score represents low quality of life.^[10]^ KEAT-26 is a validated Korean-translated version of EAT-26. It is 6-level Likert scale which consists of 11 items concerning anorexia, 7 items concerning binging or overeating, and 8 items concerning control of eating behavior. Higher score represents more problematic mealtime behavior.^[11]^

